## Abstract

**Background:**

Pediatric patients with cancer have limited options to self-manage their health while they are undergoing treatments in the hospital and after they are discharged to their homes. Extended reality (ER) using head-mounted displays has emerged as an immersive method of improving pain and mental health and promoting health-enhancing physical activity among a variety of clinical groups, but there is currently no established protocol for improving both physical and mental health in pediatric cancer rehabilitation.

**Objective:**

This phase I, pilot, feasibility randomized controlled trial aims to investigate the potential effects of a 14-week ER program on physical activity participation and indicators of health among pediatric patients with cancer who undergo bone marrow transplantation. An ancillary aim is to evaluate the feasibility of the program through participant engagement.

**Methods:**

This study includes a 2-arm parallel group design with a 1-group crossover (the control group will start the intervention after a waiting period). Overall, 16 pediatric patients with cancer undergoing rehabilitation (aged ≥8 years) at a children’s hospital will be randomly allocated into one of two groups: (1) an immediate start group that undergoes an ER program in the hospital until discharge and then for 8 weeks at home (total duration of approximately 14 weeks), and (2) a waitlist control group that undergoes usual care in the hospital and for 8 weeks at home, before receiving the 8-week home ER program. The program will include active video gaming with rhythmic music exercises as well as mindfulness-based practices using a high-quality app. Home-based programming will include behavioral coaching calls. Physical activity will be measured daily through step counts using a tri-axial accelerometer. Health outcomes will be measured across time and include global health, measured by the National Institutes of Health Patient-Reported Outcomes Measurement Information System (PROMIS) Pediatric Global Health Scale Short Form 7+2, and lung function, measured by a forced expiratory volume using a peak flow meter. Feasibility will be evaluated through participant engagement metrics, such as enrollment, dropout, adverse events, and attendance rates. Descriptive statistics will be obtained for all study variables. Outcomes will be modeled using mixed modeling procedures, and changes in means will be estimated with CIs.

**Results:**

The study was funded in February 2024. Recruitment procedures started on June 27, 2024. All data are anticipated to be collected by February 2026. Full trial results are anticipated to be analyzed and submitted for publication by March 2026. The study’s anticipated end date is March 31, 2026.

**Conclusions:**

This trial tests an accessible remote program for improving both physical and mental health among pediatric patients with cancer. The knowledge obtained from this study will inform the development of a larger trial.

**Trial Registration:**

ClinicalTrials.gov NCT06298357; https://clinicaltrials.gov/study/NCT06298357

**International Registered Report Identifier (IRRID):**

DERR1-10.2196/64879

## Introduction

### Overview of Pediatric Cancer and Physical Activity

Pediatric cancer is estimated to impact roughly 400,000 children and adolescents aged 0 to 19 years worldwide annually [1]. In the United States, it is estimated that there are about 77,000 new diagnoses each year, making up approximately 5% of all cancer cases [2]. Pediatric cancer encompasses malignancies occurring in individuals aged 19 years and younger, affecting various organs or tissues, which necessitate specialized diagnosis, treatment, and long-term follow-up care [3-5]. Notably, pediatric cancer and its treatments can diminish physical activity in children, resulting in reduced mobility, muscle weakness, fatigue, and impaired physical function [6]. Reduced activity increases their vulnerability to accelerated frailty, secondary diseases, mortality, and mental health issues, all of which can be mitigated through regular physical activity participation [7-9]. Disappointingly, physical activity levels among pediatric cancer survivors are far lower than those observed among the general pediatric population [10], which places them at high risk for cardiometabolic disease [11,12].

### Role of Aerobic Exercise in Bone Marrow Transplant Rehabilitation

Bone marrow transplant (BMT) is an effective option for treatment among patients with hematological disorders, including leukemia [13,14]. However, this treatment has been associated with poor outcomes, specifically decreased cardiorespiratory capacity for months after treatment [15,16], and this leads to compromised rehabilitation, participation in daily activities, and quality of life. A systematic review has found 25 randomized controlled trials (RCTs) demonstrating that exercise is safe and critical for improving posttreatment outcomes among adult patients with cancer after BMT [17], but far fewer studies exist for children and adolescent patients [18-20]. Starting an early exercise regime in the hospital is likely beneficial for optimizing health at admission to prepare the body for BMT, as well as for preventing physical deconditioning that can occur while admitted due to an immunocompromised status requiring isolation. However, there is a paucity of physical activity research among pediatric patients with BMT [21-24].

### Adulthood and Health Conditions

The transition from adolescence to adulthood is crucial for adopting healthy lifestyle behaviors, including physical activity, to manage and prevent health conditions. Pediatric cancer survivors have a high rate of severe, disabling, or life-threatening health conditions that can occur years after treatment [25]. In contrast, increased cardiorespiratory fitness and physical activity levels among pediatric cancer survivors have been linked with positive outcomes, such as a lower risk of obesity and cardiometabolic complications, improved overall health-related quality of life and social function, less cancer worry, and improved mental health (eg, cognitive function, depression, and self-body image) [26,27]. Another key impetus for promoting physical activity is to treat, manage, and prevent accelerated frailty that occurs among pediatric cancer survivors. The prevalence of frailty among this group has been found to be like that among adults 65 years and older [28].

### Limited Physical Activity Options and Gaps in Knowledge

Research findings addressing physical activity interventions are nonconfirmatory and are not generalizable to the general pediatric cancer population. A recent scoping review identified only 8 RCTs of physical activity for pediatric cancer survivors [29]. A systematic review identified only 2 studies that were of high enough quality to be reviewed, indicating a need for large RCTs [30]. Hospital physical activity programs have been promising but sparse [21-24]. The limitations of these studies included small sample sizes, underpowered study designs, in-person supervision by a specialist that is difficult to access in real-world settings, and limited accessible modalities for individuals with restricted mobility and functional capacity. Moreover, the modalities of aerobic exercise training were primarily walking, jogging, and bicycling, which are difficult to perform for patients with cancer who are in the early stages of treatment recovery, are in concomitant infection isolation, are severely deconditioned, or have mobility impairments. There is a dire need for early hospital physical activity modalities that are low burden on hospital staff, which can be delivered across multiple sites to improve health outcomes among pediatric patients with cancer who undergo BMT.

### Special Needs for Physical Activity

Physical performance limitations are prevalent among pediatric cancer survivors [6]. Relevant to physical activity performance, cancer survivors have poor ambulatory function [31,32] and energy expenditure [6], and have 24% greater odds of a mobility disability [31], all of which make prolonged walking and cycling difficult to perform for prolonged periods. Given that improvements to cardiometabolic health require gradual physiological adaptations following 1-3 months of exercise training [33-35], it is important to identify programs that are not only enjoyable and accessible but also effective in maintaining the interest of pediatric cancer survivors while addressing the varied needs within this group. There is an even greater need for those who undergo surgery, radiation therapy, or chemotherapy who have experienced damage to body structures or system functions and have the greatest risk for physical disability [6]. To address this need, two lessons can be learned from the field of adapted physical activity, which represents physical activity and exercise participation among people with disabilities. First, the field includes over 30 years of research in modifying and developing exercise movements and techniques to accommodate a wide variety of functional needs [36]. Second, RCTs have transitioned from a focus on multisite, supervised, in-person interventions to remote telehealth delivery [36], accommodating the low density of people who live near disability exercise specialists. Before this change, average sample sizes were 30 people per trial [36]; this is similar to current physical activity trials in pediatric cancer rehabilitation [29].

### Active Video Gaming is an Accessible and Serious Exercise

A promising area of study is the incorporation of active video gaming technology with telehealth procedures. A key benefit of active video gaming is that it provides a high level of enjoyment for children and youth. Active video gaming using an extended reality (ER) head-mounted display, the Meta Quest 3 (Reality Labs), has emerged as a promising active video gaming alternative due to its affordability and high-quality visual experiences in both virtual reality (the person is immersed in a digital environment) and mixed reality (digital objects and environments are projected into the real world through pass-through cameras). Studies have demonstrated that active video gaming with the Quest 2 (a fully virtual reality device) can achieve moderate exercise levels and provide a safe activity for various user groups, including child wheelchair users [37] and patients in intensive care [38]. In addition, virtual reality programs with psychological intervention have been found to be easy to use in clinics [39] and can improve psychological well-being among patients with cancer [40,41], which is critical given the psychological distress that can occur during and after cancer treatment [42,43]. However, to the best of our knowledge, there is no program that includes both mental health and physical activity in an intervention designed for deconditioned pediatric patients with cancer, particularly while supporting the transition across admission, BMT, and home.

### Telehealth Coaching Enhances Adherence

Home-based telehealth programs that incorporate “virtual” behavioral coaching (telecoaching) are a desirable approach for promoting nonsupervised exercise behavior within the community. Telehealth interventions that use remote communication technology bypass barriers related to lack of access, time, and nearby specialists, which are common for both children with disabilities [44] and those who have had cancer [45,46]. According to the Supportive Accountability Theory [47], programs that use telehealth technology can foster strong intervention adherence by providing a sense of accountability through remote monitoring and strong relationships with specialized health professionals. The addition of behavioral coaching strategies such as goal setting, confidence building, setting reasonable expectations, and understanding benefits, underpinned by theories such as the Social Cognitive Theory [48], have been found to enhance the likelihood of promoting exercise behavior among people with disabilities [49] and cancer survivors [50]. Social Cognitive Theory provides a targeted approach toward promoting exercise behavior through 4 constructs: self-efficacy (perceived control over one’s behaviors), outcome expectations, sociostructural factors (facilitators and barriers), and goals [48,51]. A physical activity intervention that uses telehealth technology, active video gaming in the ER, and a minimal dose of behavioral coaching has the potential to promote sustainable exercise behavior among large groups of pediatric cancer survivors.

This study tests a nearly full telehealth protocol with an ER program that includes physical activity and mental health intervention using “off-the-shelf” supplies. The study will inform a larger RCT through the following aims: (1) to examine the preliminary effects of an 8-week ER gaming telehealth program on physical activity participation among 16 pediatric patients with cancer after transplantation; (2) to explore potential program effects on key physical and mental health outcomes; and (3) to evaluate the feasibility of the program and its telehealth delivery through acceptability and safety.

## Methods

### Study Design and Overview

This phase I pilot feasibility RCT will include a 2-arm, parallel-group design to examine the preliminary effects of an ER telegaming intervention on physical activity levels among pediatric patients with cancer from a children’s hospital, compared with a waitlist control (WC). The design also includes a single-group crossover, where the WC group will receive the ER intervention after their designated wait period. The design is displayed in Figure 1. The project will include 16 pediatric patients with cancer from a single hospital who will complete the study (enrollment targets are 8 in year 1 and 8 in year 2).

This study has 2 groups, an immediate start (IS) group and a WC group. The IS group will start the intervention as soon as possible (ideally, pretransplantation within admission for BMT). Once the IS group is discharged from the hospital, they will continue the 8-week intervention at home with remote telehealth support. The anticipated hospital stay will last approximately 6 weeks. Thus, the total duration of time for the IS group will be 14 weeks (6 weeks in the hospital and 8 weeks of home intervention). The WC group will undergo the usual care within the hospital (approximately 6 weeks) and for 8 weeks after they are discharged. A total of 8 weeks after hospital discharge, WC participants will start the same 8-week intervention provided to the IS group. Data will be collected remotely throughout the study through digital monitoring technology and remote testing procedures. The total duration for WC participants in the study will be 22 weeks.

**Figure 1 figure1:**
[figure not shown]
Study procedures for both the immediate start and waitlist control groups.

### Participants

The inclusion and exclusion criteria are listed in Textbox 1.

Inclusion and exclusion criteria.
**Inclusion criteria**
Patient at the children’s hospital where the study is being conducted≥8 years of ageMedical diagnosis of malignancy or nonmalignant condition requiring hematopoietic stem cell transplantA caregiver who can assist the child with the study surveys and formsAccess to a Wi-Fi Internet connection in the home through mobile phone or tablet computer
**Exclusion criteria**
Complete blindness or deafnessInability to operate the handheld controllersSusceptibility to motion sickness in extended realityInability to communicate in English

### Screening and Recruitment

Pediatric patients with cancer are recruited from cancer clinics within the pediatric hematology-oncology department of the hospital. The recruitment strategy is physician referral through word of mouth and study flyers. Specifically, a pediatric cancer rehabilitation medicine physician team member will attend weekly BMT team meetings to scout for potentially suitable patients for the study. Prospective participants will be referred in the team meeting to the rehabilitation medicine physician, who will inform the research staff to approach the patient in their room for screening and recruitment. Research staff will screen prospective participants for the eligibility criteria and obtain informed consent and assent for participation.

### Randomization and Clinical Trial Considerations

Participants will be randomized into 1 of 2 groups—IS or WC (8 per group)—with a 1:1 allocation ratio using a permuted block randomization approach. Participants will be evenly stratified into the IS or WC group based on sex. The randomization sequence will be generated by the project statistician using a computer-generated random schedule in a permuted block (SAS, SAS Institute Inc., version 9.4). Data will be entered into a secure electronic database (REDCap [Research Electronic Data Capture], Vanderbilt University) by a research assistant. The project manager will unfold the randomization sequence for successfully enrolled participants into 1 of the 2 groups. Study outcomes will be assessed by a research assistant who will be blinded to group allocation (single-blinded trial design).

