### Statistical Analysis

Descriptive statistics, including means, SDs, and CIs, will be obtained for all study variables, and longitudinal smoothed scatterplots will be examined to identify temporal trends between groups, including the presence of potentially important nonlinear time trends. For aim 1 and aim 2 (measures of outcomes), outcomes will be modeled using all available measures, using mixed models with each participant included as a random effect to account for the repeated measures. Changes in means will be estimated with confidence intervals and compared between groups at 5 time points, which are baseline (week 0), posttransplant, hospital discharge (~week 6), midintervention or wait period (week 10), and postintervention (week 14) using estimated marginal means (also called least squares means). For aim 3, estimates with 95% CIs will be obtained for enrollment, dropout, and adverse event rates. Statistical tests will be 2-sided and will be performed using a significance level of *P*<.05. Statistical analyses will be performed using R (R Development Core Team) version 4.3.1 or higher (R Foundation for Statistical Computing).

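### Baseline is listed as a between-group comparison point and no adjustment for baseline or sex is named; for the two health outcomes this costs precision if the baseline to follow-up correlation is low to moderate

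*Protocol article*

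**What the plan says.** Under Randomization and Clinical Trial Considerations, participants go to "IS or WC (8 per group") "with a 1:1 allocation ratio using a permuted block randomization approach". Sex is the only stratification factor: "Participants will be evenly stratified into the IS or WC group based on sex".

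Under Statistical Analysis, Aim 1 and Aim 2 outcomes are analysed "using mixed models with each participant included as a random effect to account for the repeated measures". The treatment comparison is then fixed: "Changes in means will be estimated with confidence intervals and compared between groups at 5 time points, which are baseline (week 0"), followed by posttransplant, discharge, week 10 and week 14, all through estimated marginal means. Tests are two-sided at the 5% level. The section names no fixed-effect covariate.

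Under Aim 2: Health Outcomes, the PGH-7+2 and lung function are first measured at week 0. Under Aim 1, the step counter is worn from joining the study. No separate wear period before randomization is described.

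**The concern.** Listing week 0 among the between-group comparisons is faulty on either reading of the sentence. If the quantity is change, it is zero for everyone at week 0. If it is the mean, any gap at week 0 arose by chance through randomization, and a test of it says nothing about the program.

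The sentence also points to an analysis in which baseline is one more outcome, each arm has its own baseline mean, and the effect is a difference in change. That gives up the knowledge that the true baseline difference is zero. Subtracting a noisy baseline in full is less efficient than weighting it by its correlation with the outcome. With 8 patients per arm, a sizeable chance gap at baseline is likely, and part of it carries into the change contrast.

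The trial is meant to inform a larger one, so the width of its effect intervals matters. Separately, a factor used to stratify the randomization should normally appear in the model.

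**Working it through.** **Inputs from the article.** 16 patients ("The project will include 16 pediatric patients with cancer from a single hospital who will complete the study"), 8 per arm, 1:1, two-sided 5%, five common visits, a random intercept per participant. No power, effect size, SD or correlation accompanies the 16, so there is no figure of the plan's own to reproduce. Results below are in units of the outcome SD.

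**Assumed.** Correlation r between baseline and follow-up from 0.3 to 0.9; share R² of outcome variance explained by sex from 0 to 0.2; equal variance at each visit; sex balanced across arms; week-0 measurement taken before allocation is known.

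**Step 1: large-sample variance of the week-14 contrast.**
- Change from a free baseline: (2/8) × 2(1 − r).
- Baseline-adjusted or equal baseline means: (2/8) × (1 − r²).
- Ratio: 2/(1 + r).

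At r = 0.5 this is 0.250 against 0.1875, ratio 1.33. Exact generalised least squares for the random-intercept model with 16 patients and five visits gives the same values: 0.350 against 0.2275 at r = 0.3, 0.150 against 0.1275 at 0.7, and 0.050 against 0.0475 at 0.9.

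**Step 2: small-sample cost.** Estimating the baseline slope inflates the adjusted variance by 1 + 1/(16 − 4) = 13/12 and takes one degree of freedom (13 instead of 14). The ratio becomes (12/13) × 2/(1 + r).

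| r | Variance ratio, change / adjusted | 95% half-width, change vs adjusted (SD) | Power at an assumed 1 SD effect |
|---|---|---|---|
| 0.3 | 1.42 | 1.27 vs 1.07 | 35% vs 46% |
| 0.5 | 1.23 | 1.07 vs 0.97 | 46% vs 54% |
| 0.7 | 1.09 | 0.83 vs 0.80 | 67% vs 70% |
| 0.8 | 1.03 | 0.68 vs 0.67 | 84% vs 84% |
| 0.9 | 0.97 | 0.48 vs 0.49 | 99% vs 98% |

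The variances are equal when 1 + r = 24/13, that is at r ≈ 0.85.

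**Step 3: chance imbalance.** The standard error of the baseline difference is √(2/8) = 0.5 SD, so a gap of at least 0.5 SD occurs by chance about one time in three. Given a gap g, the change contrast shifts by (1 − r)g in the opposite direction: 0.5 × 0.5 = 0.25 SD at r = 0.5.

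**Step 4: sex.** A constant sex effect cancels in a within-patient change, so the change variance at r = 0.5 stays 0.250 with or without sex for R² from 0.05 to 0.2. Under a constrained baseline with R² = 0.1, the variance is 0.25 × [0.9 − (0.5 − 0.1)²/0.9] = 0.1806, against 0.1875 without sex, a reduction of about 4%. A cross-sectional week-14 contrast falls from 0.250 to 0.225. Its interval width, after the lost degree of freedom, changes by a factor of 1.007 at R² = 0, 0.98 at 0.05 and 0.96 at 0.10.

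**The case against.** The strongest reply is that the paragraph is condensed. It does not even list group and time, which the comparison needs, so the absence of sex and baseline may only mean that the covariates are set out in an analysis plan that is not shown. This stands. A reader might infer that the trial has chosen an unadjusted analysis; the article never says so. What the article does fix is the comparison of changes at five points with baseline among them, and the point rests on that.

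Second, a difference in change is unbiased under randomization, has valid intervals and already uses the baseline. This stands too. The shift in Step 3 is conditional on an imbalance that occurred and is not a bias of the estimator over repeated trials. The issue is efficiency, in a pilot that makes no power claim.

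Third, the gain depends on an unknown r. Age at entry is 8 years or over with no stated upper limit, so stable differences between patients in raw peak flow could make r high and the gain small. On the other side, week 0 is meant to precede transplant, and week 14 is at home after discharge, so a very high r should not be presumed. Adjustment gains usefully at low to moderate r and loses almost nothing at high r.

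Fourth, a reader might infer that leaving sex out wastes the precision bought by stratifying. For the change contrasts that the article describes, Step 4 shows no such loss.

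**Conclusion.** The point holds in a limited form. Week 0 should not be a between-group effect comparison, whatever the correlation. For the PGH-7 T-score and lung function, a free-baseline change contrast has about 42%, 23% and 9% more variance than a baseline-adjusted one at assumed r of 0.3, 0.5 and 0.7, with about no difference at 0.8 and a slight reversal at 0.9. These figures rest on equal variances, a random-intercept structure and a week-0 measurement taken before allocation is known.

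Two larger claims are tempting and not supported. One is that adjustment makes 16 patients worth 20 to 23. That uses the large-sample ratio over r from 0.4 to 0.6 (16/0.80 to 16/0.70) and leaves out the slope cost; with it, the range is about 18.5 to 21.1, and 16 × 1.23 = 19.7 at r = 0.5. The other is that the whole trial loses precision. The primary outcome, steps, has no stated wear window before randomization, so there is no defined baseline to adjust for and these figures do not extend to it.

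Sex belongs in the model because it was used to stratify. Any gain in precision is small and depends on sex being prognostic. This is a worthwhile improvement, not a threat to validity.

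**What to change.** In Statistical Analysis:

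1. Limit between-group effect comparisons to posttransplant, discharge, week 10 and week 14, and report week 0 descriptively.
2. For the PGH-7 T-score and lung function, either constrain the baseline means to be equal across arms in the longitudinal model or use the week-0 value as a covariate. State that week-0 measures are taken before allocation is revealed.
3. Include sex as a fixed effect in all outcome models, steps included.
4. Do not adjust steps for baseline unless a wear window before randomization is first defined.

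The cost is a few lines of text and one or two degrees of freedom. No new data are needed. If a fuller analysis plan already specifies these terms, aligning the five-point sentence with it is enough.
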